**BACKGROUND**

Infantile colic is one of the most common problems within the first three months of life. It consists of a behavioural syndrome characterized by paroxysmal, excessive and inconsolable crying without identifiable cause. Although infantile colic is commonly reported and causes appreciable distress for both parents and paediatricians, despite forty years of research, its aetiology still remains unclear. Recently the role of intestinal microflora has growing importance, and a lower count of intestinal lactobacilli has been observed in colicky infants compared to healthy ones. In a recent study we have observed that Lactobacillus reuteri improved colicky symptoms in breast-fed infants within one week of treatment compared to Simethicone, suggesting that probiotics may play a role in infantile colic (Savino F, Pelle E, Palumeri E, Oggero R, Miniero R. *Lactobacillus reuteri* (American Type Culture Collection Strain 55730) versus simethicone in the treatment of infantile colic: a prospective randomized study. Pediatrics 2007; 119:e124-30). The mechanism involved in such finding is only partially understood and, for this reason, we have planned this new study to evaluate not only the clinical improvement but also the microbiological data.

**AIM**

The aims of this study are:

- to evaluate the improvement of colicky symptoms by the oral administration of *L. reuteri:*

-primary outcome: reduction of the daily average crying time from baseline to the end of the treatment period, to less than 3 hours a day, the cut-off proposed by Wessel;

- secondary outcome: number of responders versus non-responders in each group on day 21. Responders (defined in the protocol) were those who experienced a decrease in the daily average crying time of 50% from baseline).

- to study the intestinal microflora of colicky infants before and after *L. reuteri* or placebo administration, evaluating the effect of *L. reuteri* on the growth of the main intestinal microbiota: using fluorescent in situ hybridization (FISH) (coliforms, *Clostridium butyricum*, Lactobacilli, Bifidobacteria). Further, the global intestinal microflora composition, using large-scale DNA sequencing of 16S rRNA genes ( 454-pyrosequencing technique)

At enrollment (day 0), parents will be interviewed about gestational age, type of delivery, birth weight, presence of gastrointestinal disease, and crying time. Medical examinations will be performed and growth parameters recorded at baseline and day 21. Parents will be asked to fill in a structured diary to record the daily crying time (minutes), stool characteristics and frequency and any side effects observed (constipation, vomiting and cutaneous reactions) on each day of the study. To assess tolerance, growth parameters (weight gain per day), stooling characteristics (frequency and consistency), symptoms of digestive intolerance (constipation, regurgitation or vomiting) and frequency of adverse events during the treatment period, will be evaluated. Adverse events, defined as illnesses, signs or symptoms that occurred or got worse during the course of the study, will be assessed through parental interview on their daily records. A general linear model for repeated measures will be used to assess differences in growth parameters between groups at the different time points (day 0-21). Follow-up visits will be performed by the same pediatrician on day 7 and 21. ( see FLOW-CHART)

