***Statistical analyses***

Data will be described using median and interquartile range or number and percentage for quantitative or qualitative variables, respectively. Comparisons will be made using Fisher’s exact test, Wilcoxon rank-sum test and Mann Whitney test. We will explore the structure of our data using a principal component analysis (PCA). Significance was reached with *P* < 0.01.

The analyses were performed using SAS V9.2 and Past.

Sample size was calculated to find a clinically relevant difference in the reduction in daily average crying time of 50 minutes between groups. With = .05, = .20 and an estimated standard deviation (SD) within groups of 55 minutes, 20 patients were needed per group. Twenty-five subjects per group will be enrolled to allow for a 20% drop out rate.

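### The study-wide P < 0.01 rule also covers tolerance, where it makes small to moderate harms harder to detect; differences with 95% confidence intervals would say more

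*Protocol*

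**What the plan says.** Under *Subjects and methods*, the protocol sets out what it will look at: "To assess tolerance, growth parameters (weight gain per day), stooling characteristics (frequency and consistency), symptoms of digestive intolerance", followed by "frequency of adverse events during the treatment period, will be evaluated". Adverse events "will be assessed through parental interview on their daily records".

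Only growth is given a named method: "A general linear model for repeated measures will be used to assess differences in growth parameters between groups". The same section has "growth parameters recorded at baseline and day 21", so the model has two measurement times.

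Under *Statistical analyses*, the description is fixed as "Data will be described using median and interquartile range or number and percentage for quantitative or qualitative variables, respectively". The tests are listed without being tied to outcomes: "Comparisons will be made using Fisher’s exact test, Wilcoxon rank-sum test and Mann Whitney test". One rule then covers everything: "Significance was reached with *P* < 0.01". The sample size in that section is derived from crying time alone. The *Aim* section names crying time, responders and microbiota, and does not mention tolerance.

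**The concern.** For an efficacy outcome, moving from 0.05 to 0.01 is the cautious direction. For tolerance it works the other way, because the error that matters there is missing a harm, and a stricter threshold makes that more likely. The protocol chooses a difference test for growth and applies the 0.01 rule to all analyses, so the stricter threshold reaches the tolerance data by default.

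At stake is what the trial can say about a live-bacteria product given to infants aged 4 to 16 weeks. A growth or adverse-event comparison that does not reach P < 0.01 in 20 to 25 infants per arm leaves small to moderate harms open. An interval would show which sizes of harm the data exclude; a P value above 0.01 does not.

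**Working it through.** **Inputs from the protocol (*Statistical analyses*).** 20 infants per group needed and 25 enrolled; significance at P < 0.01; sizing at 0.05 with a type II error of 0.20, a difference of 50 minutes and an SD of 55 minutes. Sidedness is not stated; two-sided is assumed.

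**The protocol's own figure.** n per group = 2 × (1.96 + 0.842)² × (55/50)² = 2 × 7.85 × 1.21 = 18.99, so 19 by the normal formula. The t-test gives 80.0% power at exactly 20. Allowing for 20% dropout, 20/0.80 = 25. The stated 20 and 25 are reproduced, and they are the arm sizes used below.

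**Assumptions.** The protocol gives no SD for weight gain and no event rates. Growth is therefore expressed in SD units of weight gain per day, and event rates are illustrative.

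**Growth.** With two measurement times and complete data, the group comparison of change can be represented by a two-sample t-test with 2n − 2 degrees of freedom and noncentrality d × √(n/2). For d = 0.5 the noncentrality is 0.5 × √10 = 1.58 (n = 20) or 0.5 × √12.5 = 1.77 (n = 25). The critical values at two-sided 0.01 are 2.71 and 2.68. Power is 14.4% and 19.3%; at 0.05 it is 33.8% and 41.0%. Chance of missing a true deficit (1 − power):

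| True deficit | n = 20, 0.01 | n = 25, 0.01 | n = 20, 0.05 | n = 25, 0.05 |
|---|---|---|---|---|
| 0.25 SD | 97% | 96% | 88% | 86% |
| 0.5 SD | 86% | 81% | 66% | 59% |
| 0.8 SD | 56% | 44% | 31% | 21% |
| 1.0 SD | 33% | 20% | 13% | 7% |

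The deficit detectable with 80% power is 1.13 SD (n = 20) or 1.00 SD (n = 25) at 0.01, against 0.91 or 0.81 SD at 0.05.

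**Adverse events, if Fisher's exact test is the one used.** Power is the sum of the binomial probabilities of all tables with P below the threshold. Chance of missing the difference:

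| Assumed rates | n = 20, 0.01 | n = 25, 0.01 | n = 20, 0.05 | n = 25, 0.05 |
|---|---|---|---|---|
| 10% vs 30% | 92% | 88% | 76% | 70% |
| 10% vs 40% | 75% | 66% | 51% | 41% |
| 10% vs 60% | 25% | 13% | 9% | 4% |

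One concrete table: 0 of 20 against 6 of 20 gives P = 2 × C(20,6)/C(40,6) = 2 × 38,760/3,838,380 = 0.020, which is not significant under the rule. At either arm size, 7 events against 0 is the smallest such split that reaches P < 0.01.

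**What intervals would show.**
- The 95% half-width for the growth difference is t(0.975, 2n − 2) × √(2/n): 2.024 × 0.316 = 0.64 SD (n = 20) or 2.011 × 0.283 = 0.57 SD (n = 25).
- With no event in an arm, the one-sided 95% upper bound is 1 − 0.05^(1/n): 13.9% (n = 20) or 11.3% (n = 25).

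**The case against.** The strongest case against is that the protocol never draws the faulty inference. Tolerance is not listed as an aim. Adverse events are only to be evaluated, and no test is assigned to them. Numbers and percentages per arm will be reported whatever the P value. Intervals for supportive safety data are usually left to the statistical analysis plan, which is not at hand, and a repeated-measures model does not prevent anyone from reporting its estimate with an interval.

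Most of this stands. A reader might infer that the plan treats non-significance as proof of safety, or that a falsely reassuring result is nearly guaranteed whatever the harm. The document supports neither. It has no rule that turns a non-significant test into a safety conclusion. Power at 0.01 is 67% to 80% for a 1-SD growth deficit and 75% to 87% for 10% versus 60%. Using Fisher's test for adverse events is also an inference from a general list.

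It is also true that the small sample drives most of the miss rate: 66% for a 0.5-SD deficit at 0.05 with 20 per arm, before the stricter threshold adds 20 points. Still, the threshold more than halves the power that remains (34% to 14% with 20 per arm, 41% to 19% with 25).

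The objection does not remove what the protocol actually fixes. It names a difference test for growth and sets a study-wide 0.01 rule with no exemption for tolerance, and an analysis plan would have to depart from that wording to put it right.

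**Conclusion.** The point holds as a minor one that is cheap to correct. Applying P < 0.01 to tolerance works in the wrong direction. With 20 or 25 infants per arm it leaves an 86% or 81% chance of missing a 0.5-SD deficit in weight gain and, if Fisher's test is used, a 92% or 88% chance of missing an assumed 10% versus 30% in adverse events. A non-significant result is therefore uninformative for small to moderate harms, but not for large ones.

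These figures rest on two-sided testing, on a two-sample comparison standing in for the growth model (adjusting for baseline would raise power somewhat), and on event rates that the protocol does not give. The absence of intervals from the protocol is not itself the error, and sizing the trial on crying time alone is not criticised here.

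**What to change.** In *Statistical analyses*, exempt the tolerance endpoints from the P < 0.01 rule and add:

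- the active-minus-placebo difference in weight gain per day, with its 95% confidence interval;
- the active-minus-placebo difference in the proportion of infants with each adverse event or intolerance symptom, with a 95% confidence interval;
- where the active arm has no event, the one-sided 95% upper bound (14% at n = 20, 11% at n = 25);
- a sentence stating that a non-significant test will not be read as evidence of tolerance.

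No formal margin is needed. On a one-sided 0.025 level, 80% power and no true difference, a 0.5-SD growth margin would take 63 infants per arm, so a test against it would usually be inconclusive here.

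The cost is a few lines of text and some intervals on data already being collected, with no added infants or visits. The drawback is a less favourable safety statement: a growth interval of about ±0.57 to ±0.64 SD may not exclude a modest deficit.

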***Statistical analyses***

Data will be described using median and interquartile range or number and percentage for quantitative or qualitative variables, respectively. Comparisons will be made using Fisher’s exact test, Wilcoxon rank-sum test and Mann Whitney test. We will explore the structure of our data using a principal component analysis (PCA). Significance was reached with *P* < 0.01.

The analyses were performed using SAS V9.2 and Past.

Sample size was calculated to find a clinically relevant difference in the reduction in daily average crying time of 50 minutes between groups. With = .05, = .20 and an estimated standard deviation (SD) within groups of 55 minutes, 20 patients were needed per group. Twenty-five subjects per group will be enrolled to allow for a 20% drop out rate.

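### Fisher's exact test is valid but conservative for the day-21 responder comparison; Boschloo's unconditional exact test would never have lower power and costs one sentence

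*Protocol*

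**What the plan says.** The statistical section gives one list of tests for all comparisons: "Comparisons will be made using Fisher’s exact test, Wilcoxon rank-sum test and Mann Whitney test". It does not assign tests to outcomes. The AIM section names the "secondary outcome: number of responders versus non-responders in each group on day 21", a responder being an infant who "experienced a decrease in the daily average crying time of 50% from baseline". That outcome is binary, and the other two entries in the list are names for the same rank test, so Fisher's test is the only listed one that fits it.

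The threshold is given as "Significance was reached with *P* < 0.01". The number of infants comes from the continuous crying-time outcome: "With = .05, = .20 and an estimated standard deviation (SD) within groups of 55 minutes, 20 patients were needed per group", and then "Twenty-five subjects per group will be enrolled to allow for a 20% drop out rate". No responder rates are assumed and no power is stated for the responder comparison.

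**The concern.** With about 20 infants per arm a two-by-two table can take few distinct values. Fisher's test also conditions on the total number of responders, which makes its null distribution coarser still. The design fixes the arm sizes but not that total. The actual chance of a false-positive responder result is therefore well below the declared threshold, and the unused part of the error allowance is paid for in power.

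An unconditional exact test uses more of that allowance without exceeding it. What is at stake is a higher chance of missing a real difference in responders, in a small trial whose threshold is already strict.

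**Working it through.** **Inputs.** From the Protocol: 20 infants per group needed and 25 enrolled, significance at P < 0.01, and a 50-minute difference with SD 55. Assumptions: two-sided testing (sidedness is not stated), .05 and .20 read as alpha and beta, two independent binomial arms, and all responder rates.

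**The plan's own figure.** The normal approximation gives n = 2 × (1.960 + 0.842)² × 55² / 50² ≈ 19.0 per group. With the t distribution, 20 per group gives 79.997% power. Allowing for the rank test, 19 / 0.955 = 19.9, so 20. For dropout, 20 / 0.80 = 25. The stated 20 and 25 are reproduced.

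**Method.** Every table (x₁, x₂) was enumerated for arm sizes n₁, n₂ from 20 to 25.
- Fisher's two-sided P, P_F, was computed for each table.
- Boschloo's P for a table is P_B = max over π of Pr(P_F ≤ observed P_F), where π is the common responder rate.
- Size is the maximum over π of the probability of rejecting. Power is the sum of the two-binomial probabilities over the rejected tables.

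**Why power cannot fall.** Fisher's test is valid at every level, so for any observed value f, Pr(P_F ≤ f) ≤ f whatever π is. Hence P_B ≤ P_F for every table, and every table that Fisher's test rejects is also rejected by Boschloo's. The enumeration confirmed this for every arm-size pair at P < 0.01.

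**Size at nominal 0.01.**

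| Arms | Fisher | Boschloo |
|---|---|---|
| 20 v 20 | 0.0046 | 0.0097 |
| 22 v 22 | 0.0047 | 0.0100 |
| 24 v 24 | 0.0055 | 0.0090 |
| 25 v 25 | 0.0050 | 0.0097 |
| All equal pairs | 0.0043–0.0055 | at most 0.0100 |
| All unequal pairs | 0.0056–0.0080 (median 0.0067) | at most 0.0100 |

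Dividing by 0.01, Fisher's test uses 43% to 55% of the nominal level with equal arms and 56% to 80% with unequal arms.

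**Power at P < 0.01, Fisher to Boschloo.**

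| Illustrative rates | 20 v 20 | 25 v 25 |
|---|---|---|
| 32.5% v 67.5% | 25.4% to 32.3% | 36.5% to 43.3% |
| 50% v 85% | 32.1% to 42.3% | 43.7% to 54.6% |
| 60% v 90% | 24.9% to 36.0% | 34.0% to 45.2% |

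The first pair is Φ(∓50 / (2 × 55)) = Φ(∓0.4545), the widest gap that a normal 50-minute shift with SD 55 gives at a fixed cut-off. It is only illustrative, because the Protocol defines response as a percentage reduction.

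**Spread of the gain at P < 0.01.** Eight rate pairs were used (20% to 60% against 60% to 90%).
- Equal arms: 2.6 to 12.7 points, median 8.1. The low end is at 24 v 24.
- Unequal arms: median about 4, mostly between 0 and 9, with extremes of 0.1 and 11.1.

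**At 0.05.** Fisher's size is 0.0253 at 20 v 20, 0.0328 at 25 v 25 and 0.0444 at 24 v 25. For 32.5% v 67.5% the gain is 1.4 points at 25 v 25 (65.3% to 66.7%) and 0.1 points at 24 v 25.

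**Example.** Take 6/20 v 15/20, so 21 responders among 40. One tail is [C(20,6)C(20,15) + C(20,5)C(20,16) + C(20,4)C(20,17) + …] / C(40,21) = 0.00458 + 0.00057 + 0.00004 + … = 0.0052. Doubled, since the arms are equal, Fisher's P = 0.0104. Boschloo's P = 0.0064. The two fall on opposite sides of the Protocol's threshold.

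**The case against.** Fisher's test fits a two-by-two table, controls the type I error and is a standard choice for small samples. Nothing in the Protocol contradicts its use, and its link to the responder outcome is inferred. All of this stands, so a reader who infers that the Protocol specifies a wrong or invalid test would go too far.

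A reader might also infer that the true error is about half the declared level, and that 7 to 12 points of power are lost, throughout the range of 20 to 25 infants per arm. The documents do not support that. Allocation is in random blocks of varying size and 20% dropout is expected, so exactly equal analysed arms are not assured. At 20 v 21 Fisher's size is already 0.0066, and the gain for 60% v 90% is 0.4 points.

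The responder rates are assumptions too. Two of the three pairs tabulated exceed what a normal 50-minute shift allows: from 50% it reaches about 82%, not 85%, and from 60% about 88%, not 90%. With those values the gains at 20 v 20 are 8.3 and 9.4 points instead of 10.2 and 11.1. This changes the size of the gain but not its direction, which holds for any rates.

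Nor is Fisher's conditioning worthless. If treatment changes no infant's outcome, the total number of responders is the same under any allocation, so conditioning on it has a randomisation rationale (approximate under blocking). Boschloo's test relies on a binomial model instead. That is a real but small price.

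**Conclusion.** The point holds as a cheap gain in efficiency on a secondary outcome for which no power is stated. At P < 0.01 Fisher's test spends 43% to 55% of the permitted error with equal arms and 56% to 80% with unequal arms. Boschloo's test stays within the level and never has lower power.

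The likely gain at P < 0.01 is about 2.5 to 12 points with equal arms (about 7 to 11 at 20 v 20 for the three illustrative pairs) and about 0 to 9, often about 4, with unequal arms. At 0.05 it may be negligible. These sizes rest on two-sided testing, binomial arms and assumed responder rates. That power is never lower does not depend on the rates.

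The use of .05 for the sample size against P < 0.01 for significance is a separate matter and costs more: at 0.01 the primary comparison has about 57% power by the t test with 20 per group.

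**What to change.** Before unblinding, add a sentence to the statistical section naming Boschloo's two-sided unconditional exact test, with Fisher's two-sided P as its statistic, for the day-21 responder comparison. Apply it at the single significance level the sponsor settles on. Report the responder risk difference with an exact unconditional confidence interval. Fisher's P may be kept as a supporting figure.

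The cost is that one sentence and a little programming. No infants, visits or data are added. The drawbacks are that the test is less familiar to readers, that it may need software other than the packages named, and that it rests on a binomial model rather than on conditioning on the total number of responders. The timing matters, because a change of test after unblinding would look driven by the data.

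### The trial is sized at alpha 0.05 but significance is declared only at P < 0.01, which cuts the stated 80% power to about 57%

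*Protocol*

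**What the plan says.** Both levels stand in the protocol's Statistical analyses section. After listing the planned tests (Fisher's exact, Wilcoxon rank-sum, Mann-Whitney) and an exploratory principal component analysis, it gives the decision rule: "Significance was reached with *P* < 0.01". No endpoint is named or excluded.

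The sample-size paragraph then targets a "clinically relevant difference in the reduction in daily average crying time of 50 minutes between groups". Its inputs read "With = .05, = .20 and an estimated standard deviation (SD) within groups of 55 minutes, 20 patients were needed per group". The Greek symbols were lost when the PDF was read, and the two values are evidently alpha and beta. The paragraph ends: "Twenty-five subjects per group will be enrolled to allow for a 20% drop out rate".

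The Aim section makes the reduction in daily average crying time the primary outcome, so the sample size concerns the primary comparison. Nothing in the protocol reserves 0.05 for that outcome, restricts 0.01 to the microbiota work, or describes 0.01 as a multiplicity adjustment.

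**The concern.** A power statement is valid only for the threshold at which the test will be judged. Here the trial is sized at 0.05 and judged at 0.01, so the 80% does not apply to the test the protocol describes. A real benefit of the size the protocol itself calls clinically relevant would be missed far more often than the planned one time in five.

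The conflict also leaves the main conclusion open. A primary P value between 0.01 and 0.05 would be positive by the sizing alpha and negative by the decision rule. The protocol gives no basis for choosing between them, and the choice should not be made after the result is known.

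**Working it through.** **Inputs**, all from Statistical analyses: difference 50 minutes; within-group SD 55 minutes; alpha 0.05 and beta 0.20 for sizing; threshold 0.01 for the decision; 20 evaluable and 25 enrolled per group. Sidedness is not stated and is inferred in step 1. The standardised difference is d = 50/55 = 0.909.

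**1. Reproduce the plan's figure.**
- Normal approximation: n = 2(SD/difference)²(z₁₋α/₂ + z₁₋β)² = 2 × 1.1² × (1.960 + 0.842)² = 2.42 × 7.849 = 18.99, so 19 per group.
- t-test at n = 20: the noncentrality is d√(n/2) = 0.909 × √10 = 2.875. The two-sided 0.05 critical value on 38 df is 2.024. Power is 79.997%, or 80% as stated.
- One-sided 0.05 would need only 15 (normal approximation) or 16 (t-test), and so does not give 20.
- Drop-out: 20/0.80 = 25, as stated.

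The sizing is therefore correct, and it was done at two-sided 0.05.

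**2. Keep everything and change only the threshold to two-sided 0.01.**
- n = 20: critical value 2.712 against the same noncentrality 2.875. Power is **56.9%**.
- n = 25 (no drop-out): noncentrality 0.909 × √12.5 = 3.214, critical value 2.682 on 48 df. Power is **70.1%**.

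**3. Sample size needed at 0.01 for 80% power.**
- Normal approximation: 2.42 × (2.576 + 0.842)² = 2.42 × 11.68 = 28.3, so 29 per group.
- t-test: 29 per group gives 78.3% and 30 gives 80.1%, so **30 evaluable** per group. With 20% drop-out, 30/0.80 = 37.5, so 38 enrolled per group.

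**4. Detectable difference.** Solving the t-test power for 80% at 0.01 with 20 per group gives **62.2 minutes**, against the planned 50.

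**5. The planned rank test.** The protocol plans Wilcoxon/Mann-Whitney tests, so power was also simulated (20,000 samples per case, 50-minute shift, SD 55, normal data).

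| Evaluable per group | Power at 0.05 | Power at 0.01 |
|---|---|---|
| 20 | about 78% | about 53% (54% with exact P values) |
| 25 | about 86% | about 67% |

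On normal data the rank test needs about 32 evaluable per group for 80% power at 0.01, or 32/0.80 = 40 enrolled.

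The rank-test result depends on the shape of the data. With the same shift and SD, 20 per group and a threshold of 0.01, simulated power was about 61% for a mildly skewed gamma (shape 4), 65% for t with 5 df, 68–70% for Laplace and gamma (shape 2), and 80% for an exponential.

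**The case against.** The strongest objection concerns scope. The P < 0.01 sentence directly follows the principal component analysis, while the only paragraph that mentions crying time uses .05. The authors may have meant 0.01 for the many microbiology comparisons and 0.05 for the primary outcome, in which case no power is lost. That intent is plausible, but the protocol does not state it. Principal component analysis yields no P value of its own, so the rule attaches to the comparisons listed just before it, and those are not limited to microbiology.

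Three further points have some force:
- **Rank-test power depends on distribution.** The figure of about 53% assumes normal data, while the protocol summarises data by median and interquartile range. Among the shapes tried, the normal was the least favourable. All but the extreme exponential stay clearly below 80% at 20 per group. The protocol sized the trial on a mean difference and SD, and on that basis the shortfall is the t-test's 23 points.
- **The worst case needs full drop-out.** Missing a 50-minute effect nearly half the time requires the whole 20% loss. With all 25 evaluable the miss rate is about 30% (t-test) to 33% (rank test, normal data), still well above 20%.
- **A stricter threshold does not inflate false positives.** This is true, but the stated power is then wrong and the primary decision rule remains ambiguous.

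The section also says in the past tense that significance was reached and analyses were performed, so the text may have been edited late. That is a reason to establish which level was prespecified before choosing the looser one.

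**Conclusion.** The concern holds. The sample-size arithmetic is right for two-sided 0.05, but the decision rule as written is 0.01, and no text reconciles the two. If 0.01 governs the primary comparison, the planned 20% type II error becomes about 43% by t-test and about 47% by rank test on normal data. Full retention does not bring power back to 80% on the plan's own basis.

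The result assumes two-sided testing (inferred because it alone reproduces 20 per group), the protocol's difference and SD, equal groups and, for the 20-per-group figures, the full 20% drop-out. Only the protocol was available. A statistical analysis plan might state a single level, but the contradiction in the protocol would still need correcting. It must be fixed because the conclusion on the primary outcome can turn on which threshold applies.

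**What to change.** First confirm from dated records which level was prespecified for the primary outcome, and settle it before the code is broken. Then choose one route:

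- **Preferred, if consistent with those records:** state that the single primary comparison of crying time is tested at two-sided 0.05, matching the sample size, and limit P < 0.01 (or a false-discovery rule) to the microbiology comparisons. This costs one sentence and no added infants.
- **If 0.01 is kept for the primary outcome:** restate the power as about 57% at 20 evaluable per group (about 53% with the rank test, assuming normal data) and about 70% if all 25 are evaluable (about 67% with the rank test). This adds no infants but makes the stated power less favourable.
- **If both 0.01 and 80% power are wanted:** re-size to 30 evaluable per group by t-test, or 38 enrolled. For the rank test on normal data the figures are about 32 and 40. That is 13 to 15 more infants per group than the planned 25.

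Whichever route is taken, state that the alpha is two-sided.
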